## Abstract

**Background:**

Neuropathic pain is common in cancer survivorship and is one of the most distressing symptoms for patients previously treated for head and neck cancer. Persistent neuropathic pain, when it is ongoing and uncontrolled, has a detrimental effect and erodes patients’ quality of life. Patients treated for head and neck cancer are chronic opioid users to manage their post-treatment pain, which may entail an increased risk of addiction and overdose. We propose to evaluate the analgesic activity of high-concentration capsaicin patches for the treatment of head and neck cancer survivors presenting with neuropathic pain sequelae.

**Methods:**

TEC-ORL is a parallel, multicenter randomized comparative phase II study evaluating whether Capsaïcin patches (Qutenza®) reduce neuropathic pain when compared to Amitriptyline (Laroxyl®) in head and neck cancer survivors presenting with neuropathic pain sequelae. The primary efficacy outcome is the rate of patients with a pain reduction of at least two points at 9 months compared to baseline. Assuming that 5% of patients become lost to follow-up, 130 patients will need to be randomized to detect a 25% improvement (i.e., standard: 25%, experimental: 50%) using a one-sided chi-square test with an alpha of 0.05%. According to the recommendations for comparative phase II trials, the target differences and type I error rates are relaxed. Randomized patients will either be treated with a capsaicin 8% (Qutenza®) patch applied at three time intervals in the experimental arm or with Amitriptyline (Laroxyl®) (oral solution 40 mg/ml) taken for 9 months at the recommended daily dose of 25 mg to 75 mg in the control arm.

**Discussion:**

TEC-ORL is a randomized comparative phase II trial designed to comprehensively evaluate the analgesic activity of capsaicin compared to Laroxyl in Head and Neck Cancer survivors presenting with neuropathic pain sequelae.

**Trial registration:**

ClinicalTrials.gov identifier: NCT04704453 Date of registration: 2021/01/13.

## Background

After curative cancer treatment, pain may affect up to 40% of cancer patients in remission [1]. In the specific case of head and neck cancer, persistent pain remains a significant problem with 45% of survivors reporting pain and 10% severe pain [2]. Head and neck cancer treatment encompasses multiple therapies (surgery, chemotherapy and/or radiation) and may produce pain by damaging somatic tissues and nerves. The prevalence of persistent pain is similar for patients treated by surgery and/or radiotherapy [3]; and chemo-radiotherapy appears to increase the frequently of chronic pain [4]. For patients treated by chemo-radiotherapy, pain is predominantly of neuropathic origin which is defined as pain caused by a lesion or disease of the somatosensory nervous system and associated with prominent symptoms such as burning, electric shock, tingling and itching sensations [5]. Persistent and uncontrolled neuropathic pain, has a detrimental effect and erodes patients’ quality of life. The pathophysiological intricacies of neuropathic pain are yet to be fully understood; its management is multifaceted and remains a challenge [6]. Treatment algorithms are distinct from those for nociceptive pain and are based on non-opioid and opioid treatments [6, 7]. Guidelines recommend amitriptyline as a first-line treatment for neuropathic pain (neoplastic or non-neoplastic) [6, 7] and for the sequalae of head and neck pain [8]. Recently, Pregabalin demonstrated a significant analgesic benefit compared to placebo in patients with head and neck cancer with radiotherapy-related neuropathic pain [9]. Pegabrilinin is yet to be adopted as a standard of care for neuropathic pain as it treats fewer symptoms than tricyclic antidepressants. Notwithstanding the efficacy of first-line therapy, some patients continue to suffer from uncontrolled neuropathic pain with only weak recommendations supporting the second-line use of lidocaine patches, high-concentration capsaicin patches, and tramadol; and a weak recommendation for strong opioids and botulinum toxin, as a third-line treatment option [6].

A recent study highlights that 50% of patient’s treated for head and neck cancer are chronic opioid users to manage their post-treatment pain [10], which may entail an increased risk of addiction and overdose [11]. It therefore seems appropriate to improve first-line treatment efficacy to spare the use of opiods in favor of other mechanisms of action. High-concentration capsaicin patches (Qtenza®) are an efficient treatment for neuropathic pain [12] and have been proposed as a second-line treatment after the failure of tricyclic antidepressant or antiepileptic treatment [6]. Caspaicin is the main active ingredient found in hot chili peppers. Pharmacologically, it is a potent and highly selective Transient Receptor Potential Vanilloid-1 (TRPV1) agonist. TRPV1 is a polymodal nociceptor which play an important role in detecting a number of pain stimuli (heat, acids etc.) [13]. Qtenza@ activates TRPV1 expressing nociceptors which cause the onset of pain and erythema. Using a process described as ‘defunctionalization’ of nociceptor fibers, cutaneous hypersensitivities are then attenuated and pain reduced [14]. Despite these interesting properties, high-concentration capsaicin patches are not recommended to treat head and neck pain. In fact, neck and face application may be associated with adverse effects (erythema, pain, irritation) due to accidental mucosa exposure. Several publications do however highlight the feasibility and potential efficacy of capsaicin treatment in this particular setting [15, 16].

Given that capsaicin treatment of the head and facial region has proven to be feasible albeit with specific warning and precaution caveats, our hypothesis is that high-concentration capsaicin patches reduce neuropathic pain when compared to Amitriptyline (Laroxyl®) in head and neck cancer survivors presenting with neuropathic pain sequelae.

## Methods and design

### Trial objectives

#### Primary objective

The primary objective of this study is to evaluate whether Capsaïcin patches (Qutenza®) reduce neuropathic pain when compared to Amitriptyline (Laroxyl®) in head and neck cancer survivors presenting with neuropathic pain sequelae.

#### Secondary objectives

Secondary objectives include a sensitivity analysis, the evolution of neuropathic pain, the safety and health related quality of life.

### Trial design

This is a Phase II, multicenter, randomized open-label and comparative study designed to evaluate whether Capsaïcin patches (Qutenza®) reduce neuropathic pain when compared to Amitriptyline (Laroxyl®) in head and neck cancer survivors presenting with neuropathic pain sequelae (ClinicalTrials.gov Identifier: NCT04704453). The primary endpoint is pain evaluated using a numeric scale. We opted for a randomized comparative phase II trial design rather than a single arm or a randomized non-comparative phase II trial to avoid obtaining false positive or false negative results only related to the study hypothesis [17]. All head and neck cancer patients presenting with neuropathic pain sequelae will be eligible for inclusion into the study. Patients that give their informed consent will be enrolled and randomized into the Amitriptyline (Laroxyl®) or Capsaïcin patch (Qutenza®) arm of the study.

### Clinical study endpoints

#### Primary endpoint

The primary efficacy outcome is the rate of patients presenting a pain reduction of at least two points at 9 months compared to baseline. Pain will be evaluated using a numeric scale from 0 (No pain) to 10 (Worst pain) by considering the average pain in the last 24 hours. Modification of a pain treatment strategy will be considered as a failure if the modification relates to neuropathic pain. Pain treatment modifications that are not related to neuropathic pain and missing values will not be considered as a failure.

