- Age ≥ 18 years. - HN cancer in remission: absence of clinical or radiological signs of progression at least 3 months after specific treatments. - Pain of the cervico-facial sphere persisting for more than 3 months after surgical and/or radiotherapy treatment. - Peripheral neuropathic character of pain objectified as a score ≥ 4/10 on the DN4 questionnaire. - Average pain intensity over the past 24 hours assessed on the numerical scale as ≥2/10. - Postmenopausal patient or patient who agrees to use effective contraception for the duration of treatment and for a minimum of 15 days after the end of the treatment period. Non-menopausal patients must have a negative pregnancy test prior to inclusion in the study. - Patient affiliated to a Social Health Insurance in France. - Patient who signed informed consent prior to inclusion in the study and prior to any specific study procedures.	- HN cancer progression. - Other concomitant neoplasia (progressive or not). - Central pain etiology. - Average pain intensity over the past 24 hours is assessed on the numerical scale as < 2/10. - Allergy to any of the components of the capsaicin patch. - Capsaicin patch cannot be applied to the area to be treated despite taking the precautions described in the protocol because of proximity to mucous membranes or eyelids. - Contraindication of amitriptyline treatment. - Patient with an unhealed skin lesion on the area to be treated. - Previous course of capsaicin or amitriptyline treatment. - Topical treatment of the painful area used for more than 21 days before inclusion. - Ongoing opioid treatment > 80 mg/day oral morphine equivalent. - Uncontrolled high blood pressure or cardiovascular history (infarction, stroke, pulmonary embolism) less than 3 months ago. - Patient included in another interventional therapeutic trial. - Pregnant or breastfeeding patient. - Any psychological, family, geographical or sociological condition that prevents compliance with the medical follow-up and/or procedures of the study protocol. - Patient who has forfeited his/her freedom through an administrative or judicial sentence or who is under legal custody (curatorship and guardianship, protection of justice).

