### Follow-up

Patients will be followed-up every 3 months from the date of randomization. Assessments will include, clinical examination, pain evaluation using the numeric scale (primary endpoint), quality of life evaluation based on the EORTC QLQ-C30 questionnaire and neuropathic pain evaluation with the NPSI. Any adverse events (AE) related to the study treatments will be collected until completion of the study.

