### Main statistical analysis

The primary endpoint will be analyzed on the Intent To Treat population and expressed as values and percentages with 95% one-sided confidence intervals. Treatment effect will be estimated using a logistic regression model adjusted for stratification factors [19]. Odds ratios will be estimated with their 95% confidence intervals (one sided). The sensitivity analysis will be conducted using a similar method. Depending on the extent of missing data, the following complementary analyses may be conducted to evaluate its influence on the results of the study: case complete study, multiple imputation for missing data.

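### The primary logistic model takes baseline pain only as a two-level stratum cut at 5, although the chance of a two-point fall depends strongly on the starting score within each stratum

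*Protocol article*

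**What the plan says.** **Endpoint** (Primary endpoint section): "The primary efficacy outcome is the rate of patients presenting a pain reduction of at least two points at 9 months compared to baseline". The scale is fixed in the same section: "Pain will be evaluated using a numeric scale from 0 (No pain) to 10 (Worst pain"). So is a composite rule: "Modification of a pain treatment strategy will be considered as a failure if the modification relates to neuropathic pain". The sensitivity endpoint uses the same two-point cut with stricter failure rules.

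**Entry** (Table 1): "Average pain intensity over the past 24 hours assessed on the numerical scale as ≥2/10".

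**Stratification** (Randomization): centre, analgesic treatment, and baseline pain in two levels cut at 5. The lower level is printed simply as 5. I read it as below 5, and I take the scale to be the 0–10 numeric scale, which that sentence does not name.

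**Model** (Main statistical analysis): "Treatment effect will be estimated using a logistic regression model adjusted for stratification factors".

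**Visits** (Follow-up): "Patients will be followed-up every 3 months from the date of randomization". The numeric scale is among the assessments at these visits. The pain measure listed among the secondary endpoints, apart from the sensitivity endpoint, is the NPSI.

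**The concern.** A fixed two-point fall is a different task at different starting scores. From 2 it needs a score of 0, a 100% reduction. From 8 it needs 6, a 25% reduction. Starting pain should therefore be one of the strongest predictors of response, yet the stated model sees only which side of 5 a patient started on. Everything that the score predicts within a stratum goes into unexplained variation, and chance imbalance between arms within a stratum is not corrected.

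At stake is some precision of the primary comparison, and an odds ratio that pools patients with very different chances of response. A related question is whether the score itself, already collected every three months, could support the reading of the responder result.

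**Working it through.** **1. The plan's own figure.** Inputs from Sample size calculation: 25% versus 50%, one-sided, 90% power, 1:1. Alpha is printed as 0.05%; I use 5%, because 0.05% taken literally would need 308 patients. With the pooled chi-square formula without continuity correction:

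n per arm = [1.645·√(2·0.375·0.625) + 1.282·√(0.1875 + 0.25)]² / 0.25² = (1.126 + 0.848)² / 0.0625 ≈ 62.3

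This is 63 per arm, 126 in total, against the stated 125. The figure reproduces. With 130 randomised and 5% lost, 130 × 0.95 = 123.5, so about 62 per arm are evaluable.

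**2. Dependence of response on starting score.** The article gives no SD or correlation, so these are assumptions: baseline mean 5, SD 2, scores rounded to integers, entry at 2 or more, baseline to month-9 correlation r of 0.3 to 0.7, and uniform shifts calibrated to 25% and 50% overall response. Simulated response, control / patch:

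| Baseline | r = 0.3 | r = 0.5 | r = 0.7 |
|---|---|---|---|
| 2 | 2% / 13% | 5% / 18% | 8% / 24% |
| 4 | 11% / 33% | 14% / 37% | 16% / 40% |
| 5 | 19% / 48% | 21% / 48% | 22% / 49% |
| 8 | 61% / 85% | 53% / 79% | 45% / 72% |
| 10 | 84% / 96% | 73% / 91% | 59% / 87% |

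At r = 0.5 the control rates averaged over the strata are about 10% (below 5) and 34% (5 or more). The split captures that contrast, but not the run from 5% to 14% inside the lower stratum or from 21% to 73% inside the upper.

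**3. Gain from adding the score to the logistic model.** Simulation at 62 per arm, baseline mean 4.5 to 5.5, SD 2, r = 0.3 to 0.7, one-sided 5% Wald tests. The type I error stays at about 5%. Power rises by roughly 0 to 4.5 points over the split-adjusted model.

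**4. What the score itself could add.**

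- *At the design effect (25% versus 50%).* The split-adjusted responder model has 90–94% power and baseline-adjusted analysis of the month-9 score has 99% or more (mean 5, SD 2).
- *At a smaller effect (25% versus 40%), uniform shift.* In closed form, the shift is z(0.40) − z(0.25) = −0.253 + 0.674 = 0.421 SD of change. Mean change has power Φ(0.421·√31 − 1.645) = 76%. Adjusting for baseline multiplies the variance by (1 + r)/2, so at r = 0.5 power is Φ(0.421·√(31/0.75) − 1.645) = 86%. The chi-square test has 55.6%. By simulation, the responder model has 57–61% and the baseline-adjusted score 79–88%. A run with other random draws gave 55–60% and 77–89%.
- *All-or-nothing response.* At 25% versus 50%, with responders falling 4 points and others not changing on average, the cut has 89% and mean change 84%. At 25% versus 40%, with responders falling 2–4 points and others unchanged or varying with SD 1, the responder model has 54–57% and the baseline-adjusted score 39–56%.

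**5. Handling of treatment changes.** The figures in step 4 contain no composite failures. At 25% versus 50%, with 10–30% failures equal in both arms:

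- Giving failures their baseline value keeps baseline-adjusted power at about 98% or more.
- Worst-rank scoring gives 91–96% at 10% failures and 82–87% at 20%, the latter below the responder test's 90%.

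With unequal failures (assumed 30% control, 15% patch, r = 0.5, 1 point of rescue benefit, 25% versus 40%), the responder model has about 66–68%, and analysis of the score ranges from 49% to 86% depending only on the handling rule.

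**The case against.** The strongest reply is that nothing here is an error. The sample size reproduces, a responder rate is a legitimate clinical summary, adjusting for the randomisation factors is standard, and minimisation balances the arms on the pain split. The dependence on starting pain does not bias the comparison, and the gain from the extra covariate is small. All of this stands, and it limits the point to an improvement. It does not remove the point: the adjustment set is a stated choice, the score is already recorded, and using it costs nothing.

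Three stronger readings are tempting and not supported.

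- *That the plan discards much of its power.* At the effect it was sized for, it has its planned 90%. The large gap appears only for smaller effects under an assumed uniform shift, and the article says that its target differences are deliberately relaxed.
- *That a true benefit below 25 points will probably be reported as no difference.* At 40% response, power is about 57–61%, so detection is more likely than not. By the pooled formula at 62 per arm, a miss becomes the likelier result only below a difference of about 14 points.
- *That the two-point cut is the only use of the numeric scale.* The article condenses a fuller protocol, and supportive or longitudinal analyses are commonly left to that document or to the analysis plan. Their absence here shows nothing.

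It is also fair to say that a repeated-measures analysis with no rule for scores after a treatment change could answer a different question from the primary endpoint. That objection is right, and the fix has to meet it.

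**Conclusion.** The point holds as a modest weakness of efficiency and interpretation in the stated primary model. Baseline pain in two levels leaves most of the within-stratum dependence of response on starting score unmodelled. The cost is roughly 0 to 4.5 power points under normal pain scores with mean 4.5–5.5, SD 2 and correlation 0.3–0.7. None of these values is in the article. The primary comparison remains valid and keeps its planned power at 25% versus 50%.

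A supportive analysis of the score is worthwhile, but its benefit is conditional: at 25% versus 40% it ranges from about 20 points or more under a uniform shift to nothing or a loss under all-or-nothing response. It also depends on the rule for treatment changes. I hold the first part with good confidence and the size of the second with moderate confidence.

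**What to change.** 1. Keep the responder endpoint as primary. In its logistic model, add baseline numeric-scale pain as a continuous covariate alongside the stratification factors, and do the same in the sensitivity analysis. The odds ratio then becomes conditional on the starting score, so report response rates by arm beside it.
2. If the full protocol or analysis plan does not already have it, pre-specify a supportive secondary analysis: the score at months 3, 6 and 9 in a mixed model for repeated measures, adjusted for baseline score and stratification factors, with the month-9 difference as the contrast.
3. State in advance how scores after a neuropathic-pain treatment change enter that analysis, consistently with the primary endpoint's failure rule. Carrying in the baseline value for failures is one example.

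The first change needs only wording and programming, with no new data and no change to the sample size. The second and third add one secondary endpoint, a little more analysis work and one estimand decision. As the trial is open-label, all three should be fixed before outcome data are examined.

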#### Secondary endpoints

The sensitivity endpoint is defined as the rate of patients presenting a pain reduction of at least two points at 9 months compared to baseline. Modification of the pain treatment strategy for any reason or patients with missing values will be scored as a failure*.

Neuropathic pain will be evaluated using the French language Neuropathic Pain Symptom Inventory (NPSI) which was developed and validated in that language [18]. The NPSI is a self-administered questionnaire specifically designed to evaluate the different symptoms of neuropathic pain.

Safety will be assessed using the toxicity grading of the National Cancer Institute (NCI-CTCAE v5).

Quality of life will be evaluated with the EORTC QLQ-C-30 questionnaire.

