### Randomization

After giving their written informed consent, patients which satisfy all the inclusion and non-inclusion criteria (Table 1) will be randomized by the sponsor at a 1:1 ratio to one of the two study arms. Randomization will be stratified according to: patient center, neuropathic pain at baseline (5 vs > =5), analgesic treatment at inclusion (no analgesic or neuropathic pain opioid treatment vs opioid treatment vs non-opioid treatment for neuropathic pain). A dynamic randomization procedure by minimization will be used. Randomization will be performed centrally by the IUCT-O clinical trials office using the TENALEA Clinical Trial Data Management System (online secure internet).

**Table 1 Tab1:** Inclusion and non-inclusion criteria

Inclusion Criteria	Non-Inclusion criteria

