### Treatment

#### Standard of care

Patients randomized to the control arm will be treated with Amitriptyline (Laroxyl®) (oral solution 40 mg/ml) taken for 9 months at the recommended daily dose of 25 mg to 75 mg.

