#### Experimental treatment

Patients randomized to the experimental arm will be treated by application of an 8% capsaicin patch (Qutenza®) at three time intervals: the first application within two weeks of randomization and the next two applications at three monthly intervals.

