Neuropathic pain is common in cancer survivorship and is one of the most distressing symptoms for patients previously treated for head and neck cancer. Neuropathic pain also decreases quality of life. There is a need to provide optimal first-line treatment to reduce neuropathic pain and to limit chronic opioid use for post-treatment neuropathic pain management [10]. To the best of our knowledge, TEC-ORL is the first randomized comparative phase II trial investigating the activity of high-concentration capsaicin patches as a first-line therapy for head and neck cancer survivors presenting with neuropathic pain sequelae.

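### The primary failure rule ignores the direction of a treatment change, so a responder who tapers a background analgesic because of relief is scored a failure, and the sensitivity endpoint repeats this

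*Protocol article*

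**What the plan says.** The protocol article, Primary endpoint, defines success as a reduction of at least two points at 9 months in average pain over the last 24 hours. It then adds: "Modification of a pain treatment strategy will be considered as a failure if the modification relates to neuropathic pain". The exemptions follow directly: "Pain treatment modifications that are not related to neuropathic pain and missing values will not be considered as a failure". No direction of change is named, and no distinction is drawn between background analgesics and the study drug.

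Secondary endpoints gives the sensitivity version: "Modification of the pain treatment strategy for any reason or patients with missing values will be scored as a failure". An asterisk closes that sentence, but the note it points to is not in the text.

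Three other places bear on the rule:
- **Randomization** stratifies by analgesic treatment at inclusion ("no analgesic or neuropathic pain opioid treatment vs opioid treatment vs non-opioid treatment for neuropathic pain"). Table 1 excludes opioid use only above 80 mg/day oral morphine equivalent. Patients can therefore enter on drugs that could later be reduced.
- **Standard of care** gives amitriptyline as "taken for 9 months at the recommended daily dose of 25 mg to 75 mg", which is a range.
- **Experimental treatment** gives three patch applications, "the first application within two weeks of randomization and the next two applications at three monthly intervals", with no range.

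**The concern.** A rule of this kind normally exists so that pain relief bought with an added analgesic is not credited to the assigned treatment. Reduction of a background drug carries no such risk. The patient must still be at least two points below baseline at month 9, now with less analgesic support. Scoring that patient a failure removes a genuine response from the numerator.

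It also sits badly with the trial's rationale, which includes the need "to limit chronic opioid use for post-treatment neuropathic pain management". The outcome that motivates the trial is one the endpoint penalises.

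A second, weaker matter is exposure by arm. If a change of amitriptyline dose within its range counts as a modification, control patients have a route to failure that patch patients do not have. The article does not say whether it counts.

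**Working it through.** **1. What the wording gives for each type of change.**

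| Change before month 9, in a patient with a fall of at least two points | Primary rule | Sensitivity rule |
|---|---|---|
| New or increased analgesic for neuropathic pain | failure | failure |
| New analgesic for another pain | not a failure | failure |
| Background opioid or neuropathic-pain drug reduced or stopped because of relief | failure | failure |
| Amitriptyline dose changed within the stated range because of neuropathic pain | not settled | not settled |

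The third row is the defect: it follows from the literal text, and both endpoints share it. The fourth row is an ambiguity. The exemption sentence speaks of pain treatment modifications in general, so the word strategy in the failure sentence does not clearly narrow the rule.

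**2. The design figure.** Inputs from Sample size calculation: 25% against 50%, one-sided chi-square test, 90% power, 125 patients, 130 randomized 1:1. Alpha is printed as 0.05%; it is read here as 5%, the value that reproduces the sample size.

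n per arm = [z(0.95)·√(2·0.375·0.625) + z(0.90)·√(0.25·0.75 + 0.50·0.50)]² / 0.25²
= [1.645·0.685 + 1.282·0.661]² / 0.0625 ≈ 62.3

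That is about 125 in total, as stated.

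**3. Effect of rescoring.** Let f be the share of true responders rescored as failures. The document gives no f, so it is an assumption. The observed rate in an affected arm is p·(1 − f). For f = 20%:
- 0.25 × 0.80 = 0.20
- 0.50 × 0.80 = 0.40

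The rejection probability is the sum of the binomial probabilities of all outcome pairs with 65 per arm for which the uncorrected one-sided 5% chi-square (pooled z) test favours the patch.

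| Scenario, f = 20% | Observed rates, control vs patch | Probability of declaring the patch superior |
|---|---|---|
| Design, no rescoring | 25% vs 50% | 90.8% |
| Both arms rescored | 20% vs 40% | 81.2% |
| Patch arm only | 25% vs 40% | 58.0% |
| Control arm only, true rates equal at 25% | 20% vs 25% | 16.9% (5% without rescoring) |

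**4. Range over f.** Normal approximation with 62.5 per arm, f = 10%, 20%, 30%:
- both arms: power about 85%, 79%, 72%, from 90%
- patch arm only: 76%, 56%, 33%
- control arm only, equal true rates of 25%: false-positive rate about 9%, 16%, 27%

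The two methods agree closely at f = 20%.

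**The case against.** **The article is a condensation.** Which changes count as a modification may be defined in the full protocol, and the note behind the asterisk is not shown. This stands in part. If a definition exists, the action shrinks to confirming and citing it. But the article does more than leave a detail out: it states the failure rule and its exemptions, and that rule as stated gives the wrong result for a tapering responder.

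**A reader might infer that the endpoint favours the patch by construction.** The text does not support that. A dose change within the range that defines the control treatment is plausibly delivery of the assigned strategy rather than modification of it. The article leaves the question open. Tapering, for its part, could fall more heavily on whichever arm works better, which would work against the patch.

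**A reader might infer a conflict with a trial objective.** Opioid sparing appears in the Background and Discussion as rationale. The primary objective is reduction of neuropathic pain, and opioid use is not among the secondary objectives. The tension is with motivation only.

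**A reader might also press two further points:** the open-label judgement of whether a change relates to neuropathic pain, and analgesics added for another pain that lower the score. The sensitivity endpoint, which fails "Modification of the pain treatment strategy for any reason", largely answers both. It does not answer tapering.

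**The figures depend on the test.** They belong to the uncorrected chi-square test. Fisher's exact test at 65 per arm gives 12.3% instead of 16.9% for the control-only case, and powers of 87.6%, 75.8% and 50.9% instead of 90.8%, 81.2% and 58.0%. The pattern is the same.

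**Conclusion.** The point holds for tapering. As worded, both the primary and the sensitivity endpoint score as a failure a patient with the required pain reduction who reduces or stops a background neuropathic-pain analgesic because of relief. Agreement between the two analyses would therefore offer no reassurance on this matter. Changes within the amitriptyline range are an unresolved ambiguity with a possible one-arm consequence, not a demonstrated bias.

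The size cannot be fixed from the document. The figures above rest on assumed shares of rescored responders, the design rates, alpha read as 5% and the uncorrected test. They show that modest shares would matter in either direction; they do not forecast a direction. The rule should be corrected before outcome data are reviewed, because in an open-label trial a definition adopted later would be less credible.

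**What to change.** Change the scoring text only; nothing here alters how patients are treated.

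- **Both endpoints:** state that reducing or stopping a background analgesic is not in itself a failure, and that changes within the assigned study regimen are not modifications.
- **Both endpoints:** keep as failure the start or increase of another neuropathic-pain analgesic, or a switch to one. Keep as failure the discontinuation of assigned treatment for lack of effect, so that this does not drop out of the rule unnoticed.
- **Sensitivity endpoint:** keep the any-reason rule for starts and increases. It then still checks the open-label relatedness judgement and analgesics added for other pain.
- **Derivation:** classify changes from a drug list together with the recorded indication, both fixed before data review. Drug and dose alone do not show which pain was being treated.

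The cost is a revision of the endpoint wording plus some programming and classification work on the concomitant-medication record. If the full protocol already contains these definitions, confirming and citing them is enough.
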